#### **Table. Dose levels of anlotinib**

| Dose levels | Usage                  | Specific amounts of drugs                      |
|-------------|------------------------|------------------------------------------------|
| 1           | 12 mg oral, once a day | 12 mg anlotinib hydrochloride capsules, 1 pill |
| 2           | 10 mg oral, once a day | 10 mg anlotinib hydrochloride capsules, 1 pill |
| 3           | 8 mg oral, once a day  | 8 mg anlotinib hydrochloride capsules, 1 pill  |

When the non-bleeding AEs occur, dose adjustment can be performed according to the table below for general principles.

**Table. The general principle of dose adjustment based on the grades of AEs**

| Grades of AEs
(NCI-CTCAE v5.0) | Time of administration                | Dose adjustment                                                                                                                                                                                                               |
|-----------------------------------|---------------------------------------|-------------------------------------------------------------------------------------------------------------------------------------------------------------------------------------------------------------------------------|
| Grade 3                           | Dose delay until recovery to grade 2  | Continue administration after a reduced dose level; if the toxicity is not recovered after 8 weeks, the treatment should be terminated permanently.                                                                           |
| Grade 4                           | Dose delay until recovery to <grade 2 | Continue administration after a reduced dose level; if the toxicity is not recovered after 8 weeks, treatment should be terminated permanently; the investigator can stop the treatment permanently judging by the treatment. |

When bleeding AEs occur, dose adjustment can be performed according to the table below.

**Table. The principle of dose adjustment in the event of bleeding AEs**

| Bleeding AEs * | Dose adjustment                                                                                                                                                               |
|----------------|-------------------------------------------------------------------------------------------------------------------------------------------------------------------------------|
| Grade 2        | Suspended administration and active symptomatic treatment; restore to <grade 2 within 8 weeks, reduce a dose level; if necessary, treatment should be terminated permanently. |
| ≥Grade 3       | Permanent termination of treatment and emergency medical intervention.                                                                                                        |

\* Bleeding AEs include hemoptysis, gastrointestinal bleeding, nosebleed, bronchial bleeding, gingival bleeding, gross hematuria, fecal occult blood, and cerebral hemorrhage.

#### Criteria for dose delay and dose adjustment of carboplatin and etoposide

Dose adjustment should be based on the severity of drug-related toxicity, which will be graded according to the NCI-CTCAE v5.0, and the potential clinical benefits in patients. A maximum of 2 dose reductions will be allowed; otherwise, treatment will be discontinued. Dose up-regulation is not considered in each patient.

When several AEs occur at the same time, the dose should be reduced according to the most severe

AE.

**Table. The general principle of dose adjustment for carboplatin and etoposide**

| Dose levels      | Carboplatin | Etoposide             |
|------------------|-------------|-----------------------|
| 1 initial dose   | AUC 5       | 100 mg/m  |
| 2 reduced dose 1 | AUC 4       | 75 mg/m   |
| 3 reduced dose 2 | AUC 3       | 50 mg/m   |

**Table. The principle of dose delay and adjustment for carboplatin and etoposide**

| AEs                                                                                                                                                                            | Dose adjustment                                                                                                                                                                                                                                                                             |
|--------------------------------------------------------------------------------------------------------------------------------------------------------------------------------|---------------------------------------------------------------------------------------------------------------------------------------------------------------------------------------------------------------------------------------------------------------------------------------------|
| ANC<1.5×10  /L and/or platelet<100×10  /L before the next dose                                                                                         | Dose delay until ANC>1.5×10  /L; platelet>100×10  /L.                                                                                                                                                                                                               |
| Grade 4 neutropenia with fever or infection, or duration ≥7 days; grade 3 neutropenia was present in the previous cycle, lasting until after day 21; grade 4 thrombocytopenia; | Intravenous infusion dose is lowered by one dose per day or the initial dose is maintained in the next dose, and G-CSF is given on day 4 (+2) of the treatment (24 hours after the carboplatin and etoposide treatment). If G-CSF does not control neutropenia, the dose should be reduced. |
| Grade 3/4 non-hematologic toxicity (excluding grade 3 nausea)                                                                                                                  | The intravenous infusion dose of carboplatin and etoposide should be reduced to one dose or the treatment should be discontinued.                                                                                                                                                           |
| Dose delay >6 weeks                                                                                                                                                            | Discontinuance.                                                                                                                                                                                                                                                                             |

Criteria for reapplying medication of carboplatin and etoposide:

(1) When drug-related AEs restore to ≤grade 1 or baseline, subjects can resume carboplatin and etoposide, excluding:

- when ANC >1.5×10^9/L, hemoglobin ≥90g/L and platelet >100×10^9/L;
- Treatment can be restarted in the event of grade 2 fatigue;
- Treatment can be restarted with grade 2 dermal toxicity and without grade 3 drug-related dermal AEs;
- Treatment can be restarted when drug-related pulmonary toxicity has returned to baseline;

(2) If the criteria for reapplying medication are not met, the next cycle of chemotherapy must be delayed. If the criteria are not met after a delayed dose of more than 6 weeks, one or both chemotherapies should be discontinued;

(3) If the next cycle of administration must be delayed due to carboplatin or etoposide-related toxicity, another chemotherapy should also be delayed.

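### Grade 4 thrombocytopenia shares a chemotherapy-adjustment row with neutropenia, so the guidance lists an unchanged initial dose with G-CSF as an option after an isolated platelet event

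*Protocol*

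**What the plan says.** All of the text is in Protocol section 5.3.2.

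- **Trigger cell.** The row opens with grade 4 neutropenia that is febrile, infected or lasts at least 7 days. It then lists, separated by semicolons, "grade 3 neutropenia was present in the previous cycle, lasting until after day 21; grade 4 thrombocytopenia". The platelet event is a trigger in its own right.
- **Action cell.** One cell serves every trigger. The first option is "Intravenous infusion dose is lowered by one dose per day". The alternative, joined by a plain 'or', is that "the initial dose is maintained in the next dose, and G-CSF is given on day 4 (+2) of the treatment". The cell closes with "If G-CSF does not control neutropenia, the dose should be reduced".
- **Neighbouring row.** For grade 3/4 non-hematologic toxicity (grade 3 nausea excepted) the action is "The intravenous infusion dose of carboplatin and etoposide should be reduced to one dose or the treatment should be discontinued". It offers no unchanged dose.
- **Platelet timing.** The first row of the table and the restart criteria below it hold the next dose until platelets exceed 100×10^9/L. On long delays the restart criteria say "If the criteria are not met after a delayed dose of more than 6 weeks, one or both chemotherapies should be discontinued".
- **General rules for the two drugs.** Adjustment follows toxicity severity, weighed with potential clinical benefit. In addition: "A maximum of 2 dose reductions will be allowed; otherwise, treatment will be discontinued" and "Dose up-regulation is not considered in each patient".
- **Status of the tables.** The general principles present them as rules that investigators may consult. Departures are allowed after discussion with the sponsor, with the reason recorded.

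**The concern.** G-CSF appears in this row as treatment for neutropenia, and the sentence that forces a reduction depends on uncontrolled neutropenia. Neither does anything for platelets. An investigator facing an isolated grade 4 platelet nadir who picks the second option follows the table as written, yet repeats the dose that preceded the nadir. The compulsory step-down can never be set off by platelets.

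The wording deserves care in this trial. Section 1.12 says that carboplatin carries more marrow suppression than cisplatin. Two of the three arms add anlotinib, for which section 1.10 lists bleeding among the common adverse events and section 1.11 reports decreased platelet count in 11.11% of treated patients (any grade). These facts show why clear platelet guidance matters here. They do not give a rate of harm.

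**Working it through.** **Step 1: is there another platelet dose rule?** Reading section 5.3.2 through:

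| Rule | What it controls after grade 4 thrombocytopenia |
|---|---|
| Pre-dose delay until platelets >100×10^9/L | Timing |
| Restart criteria, same threshold | Timing |
| Stop after a delay of more than 6 weeks | Stopping |
| Severity-and-benefit principle | General direction, no platelet-specific level |
| Two-reduction cap, no up-regulation | Bounds on reductions once made |
| Anlotinib grade 4 rule (non-bleeding events) | Anlotinib only, if the event is attributed to it |
| Shared neutropenia/thrombocytopenia row | Chemotherapy dose: lower, or keep the initial dose with G-CSF |

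Only the last row sets a chemotherapy dose after the nadir, and it does not separate the triggers. G-CSF could attach to the second option alone or to both. On either reading the unchanged dose is a listed response to a platelet event.

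**Step 2: gap between the two options at a first event.** Inputs: four induction cycles, carboplatin AUC 5 on day 1 and etoposide 100 mg/m² on days 1–3 (section 5.2.1); reduced levels AUC 4 with 75 mg/m², then AUC 3 with 50 mg/m² (dose-level table, section 5.3.2). Assumption: lowering by one dose means one level of that table.

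- Carboplatin per cycle: (5 − 4)/5 = 20% lower.
- Etoposide per cycle: 3×100 = 300 against 3×75 = 225 mg/m²; 75/300 = 25% lower.

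The choice can arise at up to three re-dosing points, before cycles 2, 3 and 4. These percentages are the dose gap between the options, not a measure of harm.

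**Step 3: dose-intensity cost of a default reduction.** The comparator is a patient who keeps the initial dose throughout: carboplatin 4×5 = 20, etoposide 4×300 = 1200 mg/m².

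| Grade 4 platelet event after cycle | Carboplatin AUC total | Change | Etoposide total (mg/m²) | Change |
|---|---|---|---|---|
| 3 only | 5+5+5+4 = 19 | −5% | 900+225 = 1125 | −6.25% |
| 2 only | 5+5+4+4 = 18 | −10% | 600+2×225 = 1050 | −12.5% |
| 1 only | 5+4+4+4 = 17 | −15% | 300+3×225 = 975 | −18.75% |
| 1 and 2 | 5+4+3+3 = 15 | −25% | 300+225+150+150 = 825 | −31.25% |
| 1, 2 and 3 | 5+4+3+0 = 12 | −40% | 300+225+150+0 = 675 | −43.75% |

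In the last line a third reduction would be needed. The cap allows two, so chemotherapy stops before cycle 4 unless a departure is documented. An earlier reduction for neutropenia would use up part of the same cap.

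**What cannot be computed.** The document gives no grade 4 thrombocytopenia rate and no frequency of choosing the unchanged dose. Neither the number of patients affected nor the harm avoided can be estimated.

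**The case against.** The strongest reply is that the row contradicts nothing else in the protocol. Reduction comes first, the closing sentence invites a clinician to read G-CSF as the neutropenia branch, and the severity-and-benefit principle makes the choice a guided clinical one. Nothing in the document says that a recovered, isolated grade 4 platelet nadir must lead to a reduction. The contrast with the non-hematologic row is only suggestive, because the table treats marrow toxicity separately and gives it its own recovery threshold.

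Much of this stands. It limits the point to wording and rules out calling the row an internal contradiction. It also means that a lower dose should be the default, open to documented departure, and not an absolute requirement.

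It does not remove the defect. The 'or' states no preference, and the likely clinical reading is not written down. The threshold and the 6-week stop govern when chemotherapy resumes or ends, not the dose given after recovery. Departing from the table calls for sponsor consultation and a recorded reason, whereas keeping the full dose needs neither.

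The objection is also right that a default reduction costs more than a single-event figure suggests. Because up-regulation is barred, each cut persists, and repeated events run into the cap.

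**Conclusion.** The point holds as a modest safety-wording defect: after an isolated grade 4 platelet event, the guidance lists an unchanged initial dose with G-CSF, although G-CSF and the only compulsory reduction in the row concern neutropenia. Correcting it is worthwhile. Its clinical size is unknown.

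A reader might infer more, and the documents do not support it:

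- *That patients are re-dosed while thrombocytopenic.* They are not; the platelet threshold applies before every next dose.
- *That the protocol directs full dose after such an event.* It only permits it, alongside reduction.
- *That an already reduced patient may return to the initial dose.* Up-regulation is barred, so the unchanged initial dose is open only to patients not yet reduced.
- *That the trial's inference is affected.* The row is the same in all three blinded arms and has no bearing on alpha, power or sample size.

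The conclusion rests on reading the semicolons as separating independent triggers. The dose arithmetic also assumes that one dose means one dose level.

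**What to change.** Edit one table row in section 5.3.2:

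1. Confine the option of keeping the initial dose with G-CSF, and its fallback sentence, to the neutropenia triggers.
2. Give grade 4 thrombocytopenia its own action: delay until platelets exceed 100×10^9/L, then by default resume carboplatin and etoposide one dose level lower.
3. Leave the two-reduction cap, the bar on up-regulation, the 6-week stop and the route for documented departures as they are.

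No new tests or visits are needed. The price is the lower dose intensity tabulated above, and only in patients who would otherwise have kept the initial dose. The edit adds no stopping rule, but combined with the existing cap it leads to discontinuation after a third event unless a departure is recorded. The amendment should say so.

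The reductions may also fall unevenly. In Supplementary Table S3, treatment-related events leading to chemotherapy reduction or interruption occurred in 50.8% and 52.5% of the two anlotinib arms against 41.1% of the control arm. If grade 4 platelet events follow that pattern, which is an assumption because no such rate is given, the default reduction would apply more often in the anlotinib arms.

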## 5.4 Disease Progression

Since similar drugs of TQB2450 induced pseudo-progression in the clinical administration, the efficacy evaluation will be assessed by RECIST v1.1 and further confirmed by iRECIST criteria. That is, patients identified as having disease progression as per RECIST v1.1 will be confirmed by iRECIST to determine further treatment.

## 6. Biological Samples

### 6.1 Serum Anti-TQB2450 Antibody (ADA) Assessment

The scheduled intervals for immunogenicity monitoring will be based on the administration time of TQB2450. If the administration time of TQB2450 is delayed, blood sampling for immunogenicity will be delayed accordingly.

For subjects with positive ADA, the neutralization antibody will be detected.

Blood samples (5 mL) will be collected pre-dose (within -15 min) at cycles 1, 2, 5, 7, and day 90 ( $\pm 7$ ) after the last administration. Samples will be collected in separation gel procoagulant tubes for 30 min and then centrifuged at 3000 g for 10 min. The obtained serum will be stored for measuring the immunogenicity and blood concentration of TQB2450. Detailed procedure is listed in the SOP provided by the central laboratory.

Additional blood samples (5 mL) will be considered for subjects with unexpected irAEs to measure the immunogenicity and blood concentration of TQB2450. However, if the time of sampling is less than 24 hours from the latest collection, the additional sampling could be exempted.

### 6.2 Biomarker Assessment

Tumor tissues will be required for the biomarkers analysis, including PD-L1 expression, tumor mutation burden (TMB) detection, etc.

Fresh biopsy tissue samples within 1 month prior to enrollment are preferred for the biomarkers analysis. One or more percutaneous punctures are required for the fresh tissue sampling procedure. If fresh biopsy samples are not available, archived tissue samples are also allowed. Ten unstained pathological tissue sections (4  $\mu$ m) are required for this study. If the sections can not be detected within 1 month, they should be embedded with paraffin. Detailed procedure is listed in the SOP provided by the central laboratory.

Blood samples (10 mL) will be collected before enrollment (within 7 days before administration) and at the end of the trial visit ( $\pm 3$  days) for the liquid biopsy-based biomarkers analysis, such as the ctDNA measurement of bTMB levels.

## 7. Assessments

### Screening

- **Assessments within 14 days before study initiation:**
  - ✓ Sign the informed consent form;
  - ✓ Collection of medical history and baseline characteristics, including subjects' ID, gender, age,

- mailing address, and telephone;
- ✓ Collection of medical history (if the initial diagnosis is ES-SCLC, the time of initial diagnosis should be recorded; if the initial diagnosis is limited-stage SCLC and developed into ES-SCLC later, two of time points should be recorded; TNM staging), and smoking history;
  - ✓ Collection of previous anti-tumor therapies (e.g., the date and types of previous surgery; the start and end date of chemotherapy and radiotherapy, best response, treatment duration, and the date of the last dose);
  - ✓ Echocardiography;
  - ✓ Screening for infection, including human immunodeficiency virus (HIV) test, hepatitis B virus (HBV) test (if HBsAg is positive, quantitative serum HBV DNA levels will be detected), hepatitis C virus (HCV) antibody test (if HCV antibody is positive, quantitative HCV RNA levels will be detected);
  - ✓ Assessment of liver function;
  - ✓ Imaging examination (CT or MRI): PET will not be used as a routine method in the imaging assessment. Enhanced CT or MRI of the chest, abdomen, and pelvis is required for all subjects before administration. For subjects with bone metastases, a whole-body bone scan should be performed. All suspected lesions will be evaluated by imaging. During the screening period, a cranial plain scan plus enhanced MRI, and bone scan is required for all subjects (However, for subjects without bone metastases, whether the bone scan is performed will be decided by the investigator according to the symptoms);
  - ✓ Collection of archived or fresh tumor tissue samples;
  - ✓ Questionnaire for health-related quality of life (HRQOL);
  - ✓ Concomitant medications and adverse events.
  - **Assessments within 7 days before study initiation:**
    - ✓ Systematic physical examination: ECOG PS, height, weight, vital signs, and physical examination;
    - ✓ Serum pregnancy test: HCG testing (applicable to women of childbearing age);
    - ✓ Serum carcinoembryonic antigen (CEA) and neural-specific enolase (NSE);
    - ✓ 12-lead electrocardiogram;
    - ✓ Hemanalysis, urinalysis and stool analysis (including occult blood), thyroid function (T3, T4, FT3, FT4, TSH), coagulation function (PT, APTT, TT, FBG, D-Dimer, INR);
    - ✓ Liver function (TP, A, G, ALT, AST, LDH, ALP, TBil, DBil, IBil), renal function (BUN or UREA, Cr, UA), blood lipid profile (TC, TG, HDL, LDL), electrolyte ( $K^+$ ,  $Na^+$ ,  $Cl^-$ ,  $Ca^{2+}$ ,  $Mg^{2+}$ , P), blood lipase, blood amylase, fasting blood glucose, etc.
    - ✓ Biomarkers of myocardial injury;

- ✓ Adrenal cortex function;
- ✓ Blood samples for liquid biopsy-based biomarkers analysis;
- ✓ Concomitant medications and adverse events.

### **Treatment Period**

#### **Cycle 1**

- Cycle 1 day 1 (C1D1):  
Vital signs and physical examination before administration;  
Concomitant medications, AEs, and medication allocation.
- C1D8:  
Vital signs and physical examination;  
12-lead electrocardiogram;  
Blood biochemistry and hemanalysis;  
Concomitant medications and AEs.
- C1D15:  
Vital signs and physical examination;  
12-lead electrocardiogram;  
Blood biochemistry and hemanalysis;  
Concomitant medications and AEs.
- C1D21:  
Vital signs and physical examination;  
12-lead electrocardiogram;  
Blood biochemistry, hemanalysis, urinalysis and stool tests (including occult blood), thyroid function, coagulation function, blood lipase, and amylase;  
Biomarkers of myocardial injury;  
Echocardiography;  
Adrenal cortex function;  
Concomitant medications, AEs, medication allocation, and recall.

#### **Cycle 2**

- Cycle 2 day 1 (C2D1):  
Vital signs and physical examination before administration;

Concomitant medications, AEs, and medication allocation.

- C2D8:

Vital signs and physical examination;

12-lead electrocardiogram;

Blood biochemistry and hemanalysis;

Concomitant medications and AEs.

- C2D15:

Vital signs, physical examination;

12-lead electrocardiogram;

Blood biochemistry and hemanalysis;

Concomitant medications and AEs.

- C2D21:

Vital signs, ECOG PS, and physical examination;

Imaging examination (CT or MRI), CEA, and NSE;

12-lead electrocardiogram;

Blood biochemistry, hemanalysis, urinalysis and stool tests (including occult blood), thyroid function, coagulation function, blood lipase, and amylase;

Biomarkers of myocardial injury;

Echocardiography;

Adrenal cortex function;

Questionnaire for HRQOL;

Concomitant medications, AEs, medication allocation, and recall.

**Cycle 3 and subsequent odd cycles (Vital signs and physical examination will be measured before administration on C3D1)**

- Day 21 on every cycle:

Vital signs and physical examination;

12-lead electrocardiogram;

Blood biochemistry, hemanalysis, urinalysis, and stool tests (including occult blood);

Biomarkers of myocardial injury;

Adrenal cortex function;

Concomitant medications, AEs, medication allocation, and recall.

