#### Pharmacokinetics of multiple doses:

Eligible subjects received anlotinib once for a single-dose clinical pharmacokinetic study. Thereafter, the pharmacokinetic study with continuous administration was initiated following a  $\geq 7$ -day wash-out period. Subjects received anlotinib on days 1-14 every 3 weeks and were monitored for at least 2 cycles. A total of 21 subjects in 3 dose groups (10 mg, 16 mg, and 12 mg) were given anlotinib and monitored the plasma concentration meanwhile. The mean time curve of each dose group was shown on the right of **Figure 1.9.2-1**. The pharmacokinetic parameters estimated were shown in **Table 1.9.2-2**.

After multiple doses, the plasma concentration of anlotinib increased along with the administration times due to the long elimination half-life of anlotinib in humans. The administration regimen with consecutive 2 weeks and stop 1 week was applied to control the plasma concentration of anlotinib following the administration. Anlotinib reached its maximum plasma concentration on day 14 following the administration regimen. The plasma concentration of anlotinib was almost  $<100$  ng/mL at the dose of 10 and 12 mg/person/day.

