**Cycle 4 and subsequent even cycles (Vital signs and physical examination will be measured before administration on C4D1)**

- Day 21 on every cycle:

Vital signs, ECOG PS, physical examination;

Imaging examination (CT or MRI), CEA, NSE;

12-lead electrocardiogram;

Blood biochemistry, hemanalysis, urinalysis and stool tests (including occult blood), thyroid function, coagulation function, blood lipase, and amylase;

Biomarkers of myocardial injury;

Echocardiography;

Adrenal cortex function;

Questionnaire for HRQOL;

Concomitant medications, AEs, medication allocation, and recall.

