### **13.5.3 Vital Signs**

The values and changes in vital signs before and after the treatment will be summarized by mean, SD, minimum, maximum, and median in each intervention arm.

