### **13.5.4 Laboratory Test Abnormalities**

Laboratory values will be descriptively summarized by the intervention arm. Quantitative variables (eg., hematology and biochemistry) will be summarized by mean, SD, minimum, maximum, and median, as well as their changes from baseline within each intervention arm.

Laboratory values will be classified into lower or higher than normal according to the range of normal values. The abnormal changes from baseline will be presented with the crosstab. The clinically meaningful abnormalities will be judged by investigators and summarized by the number and percentage.

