### **13.5.5 ECG**

ECG will be identified to be normal or abnormal by investigators' judgment. The changes from baseline in ECG will be summarized.

The values and changes from the baseline of heart rate, PR interval, QRS interval, QT interval, and QTc will be summarized by mean, SD, minimum, maximum, and median. The overall results of ECG will be presented with the crosstab. The clinically meaningful abnormalities will be judged by investigators and summarized by the number and percentage.

Listings of ECG results will be provided in each arm.

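### From cycle 3, ECGs and blood tests are scheduled only on day 21: this does not fully support the chemotherapy and anlotinib dose-modification rules, and the low/high laboratory table does not show severity

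*Protocol*

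**What the plan says.** **Visit schedule (Protocol section 7, Treatment Period).** Cycles 1 and 2 each list days 8, 15 and 21 with vital signs, ECG, biochemistry and blood counts. For cycle 3 and later odd cycles, and for cycle 4 and later even cycles, these tests are listed only at "Day 21 on every cycle". The sole additions are in the two headings: "Vital signs and physical examination will be measured before administration on C3D1" and "Vital signs and physical examination will be measured before administration on C4D1". Neither adds an ECG or a count.

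**Treatment (section 5.2.1).** Carboplatin and etoposide are given for four 21-day cycles. Anlotinib or its placebo is taken on days 1-14 of every cycle, including maintenance.

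**Exposure (section 1.9.2).** "Anlotinib reached its maximum plasma concentration on day 14 following the administration regimen". Table 1.9.2-1 gives single-dose half-lives of 95.3, 116 and 97.9 h at 10, 12 and 16 mg.

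**Dose rules (section 5.3.2).** One row of the carboplatin and etoposide table acts on "Grade 4 neutropenia with fever or infection, or duration ≥7 days; grade 3 neutropenia was present in the previous cycle, lasting until after day 21", and then on grade 4 thrombocytopenia. Another row delays the dose when neutrophils or platelets are low before the next dose. The anlotinib delay rule acts on related adverse events arising on days 1-14 of each cycle.

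**Analysis.** Section 13.5.3: "The values and changes in vital signs before and after the treatment will be summarized by mean, SD, minimum, maximum, and median". Section 13.5.4 gives quantitative summaries and changes from baseline, and then: "Laboratory values will be classified into lower or higher than normal according to the range of normal values", with shifts from baseline shown in a crosstab. Section 13.5.5: "The values and changes from the baseline of heart rate, PR interval, QRS interval, QT interval, and QTc will be summarized". Section 13.5.2 counts treatment-emergent adverse events by worst CTCAE v5.0 grade.

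**The concern.** Two things do not fit together.

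First, the dose rules in section 5.3.2 apply in every cycle, but the tests that feed them thin out after cycle 2. A rule that depends on how long a severe neutropenia lasted needs more than one count per cycle. A rule for events on days 1-14 has little scheduled support when the next visit is on day 21.

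Second, abnormal laboratory findings are a named secondary safety endpoint (section 3.6). In three arms that all receive carboplatin and etoposide, many patients can be expected to have some count below normal. A table that records only below or above normal then says little about whether adding anlotinib, or anlotinib and TQB2450, deepens cytopenia. Blood pressure and QTc matter too: the protocol's background sections report hypertension in 39.51% (phase II study in small-cell lung cancer) and 53.3% (phase II study in non-small-cell lung cancer), and prolonged QTc in 13.58% (the former study). A silent change in QTc, blood pressure or counts has to be measured before it can be recorded.

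**Working it through.** **1. Exposure on the visit days.** The last capsule is on day 14 and the visit on day 21: 7 days, or 168 h. With first-order decline, the fraction left is 2^(-168 / half-life).

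| Half-life (Table 1.9.2-1) | Fraction of the day-14 peak left on day 21 |
|---|---|
| 95.3 h (10 mg, n=4) | 2^(-1.763) = 0.29 |
| 97.9 h (16 mg, n=4) | 2^(-1.716) = 0.30 |
| 116 h (12 mg, n=11) | 2^(-1.448) = 0.37 |

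The same model puts day 8 at 79-82% of peak and day 15 (24 h after the last capsule) at 84-87%. These are the visits that cycles 1 and 2 have and later cycles lack.

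Check of the model: with q = 2^(-24 / half-life), accumulation over 14 daily doses is (1 - q^14)/(1 - q), which is 5.70 at 95.3 h and 6.48 at 116 h. Multiplied by the 12 mg single-dose peak of 10.5 ng/mL this predicts 59.9 to 68.0 ng/mL, or 61.4 to 71.4 ng/mL with carry-over from the previous cycle. Table 1.9.2-2 reports 61.6 ± 16.3 ng/mL at 12 mg, so the model is adequate for this purpose.

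The spread is wide. The 12 mg half-life is 116 ± 47 h; at one SD above the mean (163 h) the fraction left is 2^(-168/163) = 0.49.

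**2. Scheduled tests inside the cycle.** ECGs and counts on days 2-20: two in each of cycles 1 and 2 (days 8 and 15), none from cycle 3 on.

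**3. Triggers set against the scheduled cycle 3 counts.** Cycle 4 is the last chemotherapy cycle, so the only later chemotherapy decision that depends on cycle 3 counts is the one for cycle 4.

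| Item in section 5.3.2 | From scheduled tests alone |
|---|---|
| Grade 4 neutropenia with fever or infection | Works when the patient presents unwell and is tested |
| Grade 4 neutropenia lasting at least 7 days | Cannot be established from one count on day 21 |
| Grade 3 neutropenia lasting past day 21 | Can be picked up at the day-21 visit |
| Grade 4 thrombocytopenia | Seen only if still present on day 21 |
| Low counts before the next dose (delay row) | Works |
| Anlotinib-related events on days 1-14 (delay rule) | No scheduled check after day 1 in the window; same in every later cycle |

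**4. What the analysis text recovers.** The crosstab in section 13.5.4 places a grade 1 and a grade 4 neutropenia in the same cell. The quantitative summaries there include the minimum, but that is one extreme value per arm, not a count of patients by severity. Section 13.5.2 does grade events, but a laboratory abnormality becomes an adverse event under section 10.3 only if it brings symptoms, a treatment change or an intervention, or if the investigator judges it significant.

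**The case against.** The strongest reply is that the gap is small and that the rest is table detail. Only one trigger is lost to scheduled testing, for one chemotherapy decision. A missed mid-cycle count in cycle 4 governs no later chemotherapy dose. Nothing bars unscheduled tests, adverse events are recorded whenever they occur (section 10.1), and section 5.3.2 says investigators may refer to its rules. All arms share the schedule, and cycles 1 and 2 supply day-8 and day-15 data in each. Section 13.5.4 also gives quantitative summaries, section 13.5.2 reports graded events, and time points and worst-value rules usually belong to a statistical analysis plan, which is not at hand.

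Most of this stands, and it rules out several stronger readings that a reader might infer:

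- *That the chemotherapy dose rule cannot act in cycle 3.* The fever or infection trigger, the past-day-21 trigger and the pre-dose row all can.
- *That day 21 falls after counts have recovered.* No section dates the nadir or the recovery, and the rule itself foresees neutropenia beyond day 21.
- *That day 21 lies outside the period of harm, or is off-drug.* About 29-37% of peak anlotinib exposure remains, and section 1.6 gives TQB2450 a half-life of 320 h. The protocol does not show that blood pressure or QTc follows concentration within a cycle, so a bias of known size cannot be claimed.
- *That laboratory values are reported only as low or high.* The quantitative summaries and the graded adverse events are also planned.

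What does not fall is narrower. The duration trigger and the scheduled counts do not match. The day 1-14 anlotinib rule has no scheduled support from cycle 3. The low/high classification is a stated choice rather than a detail left open. The missing time points in sections 13.5.3 and 13.5.5 are not a defect in themselves; naming them is a cheap improvement.

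**Conclusion.** The point holds in a limited form. From cycle 3, scheduled ECGs and blood tests fall only on day 21, away from peak anlotinib exposure. In cycle 3 one of four cytopenia triggers cannot be established on schedule, one is seen only if it persists, and two remain workable. The anlotinib delay rule lacks a scheduled check after day 1 in its window for as long as treatment continues. The low/high crosstab does not separate mild from severe cytopenia, and graded adverse-event tables fill that gap only for abnormalities that were reported as events.

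The exposure figures assume first-order decline and use single-dose mean half-lives from small groups, so they are approximate. The reading of the triggers assumes that only scheduled tests are done; unscheduled testing would narrow the gap by an amount the protocol does not let one estimate. The matter deserves correction because it bears on safety and the analysis change is nearly free. It does not affect the primary efficacy analyses.

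**What to change.** **Section 13.5.4.** Replace or supplement the low/high crosstab for blood counts with a shift table by arm from baseline to worst CTCAE v5.0 grade, using all on-treatment counts, scheduled and unscheduled, in all cycles. Give the number of counts per patient by arm beside it, because a worst value depends on how often one looks.

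**Sections 13.5.3 and 13.5.5.** Report worst on-treatment blood pressure and QTc by arm. Show the day-15 values of cycles 1 and 2 separately from the day-21 values, and do not label day 21 as off-drug.

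**Sections 5.3.2 and 7.** The sponsor must reconcile the chemotherapy dose-adjustment table and the anlotinib delay rule with the visit schedule from cycle 3. No dose or monitoring rule is proposed here.

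**Cost.** Revised wording, extra tables from data already collected, and one protocol clarification. The limit is that worst values after cycle 2 will still rest mainly on day-21 sampling, which no analysis can undo.
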